**The following criteria lead to stop of additional CIK cell infusions; patients are remaining in the study:**

- Development of GVHD > Grade II
- Response to CIK cell therapy: If mixed chimerism was the reason for study eligibility, than the achievement of complete donor chimerism leads to the stop of further CIK cell infusions. If the inclusion into the study was favored by minimal residual disease detection, the achievement of MRD negativity leads to a stop of additional CIK cell infusions.

- Severe infections

**The following criteria lead to withdrawal from study; patients will be followed up for one month:**

- Pregnancy of female patients
- Relapse of the underlying disease during CIK cell treatment requiring other treatment (e.g. systemic chemotherapy, second stem cell transplantation)

## **8.2 Criteria for Discontinuation or Termination of the Study**

Both the sponsor and the investigator reserve the right to terminate the study at any time. Should this be necessary, both parties will arrange the procedures on an individual study basis after review and consultation. In terminating the study, the Sponsor and the investigator will assure that adequate consideration is given to the protection of the patient's interests.

Criteria, which could lead to a discontinuation or termination of the study, are:

- Safety reason regarding patients' safety
- Negative benefit/risk assessment due to new information

In case of premature termination of the study all collected data have to be analyzed and a report has to be written. The sponsor has to inform the federal regulatory authority, the ethics committees and other authorities of member states of the European Union where the study is conducted within 15 days, giving detailed reason for the premature termination.

## **9 Publications Rules and Results**

The sponsor is responsible for the timely reporting of study data – latest 2 years after last patient last visit. An integrated clinical study report (CSR) has to be completed one year after end of the study (whether completed or prematurely terminated).

The results of this study may be published or presented at scientific meetings as soon as after completion of the study. If this is foreseen, the investigator agrees to submit all manuscripts or abstracts to the sponsor prior to submission.

In a multicenter study, it must be ensured that the data from one center is not published before the publication of the whole study. The sponsor reserves the right to review the manuscript(s) before their submission for publication or presentation. This is not intended to restrict or hinder publication or presentation, but is to allow the sponsor to protect proprietary information and to provide comments based on information from other studies that may not yet be available to the investigator(s).

This study will be registered at <http://www.clintrials.gov>.

## **10 Monitoring**

To ensure compliance with the protocol and with the ethical principles of Declaration of Helsinki and GCP, selected monitoring visits for source data verification by a professional representative of the sponsor will be scheduled to take place early in the study, during the study at predefined intervals and after the last subject has completed the study. In addition it may be necessary for the sponsor or a Drug Regulatory Agency to conduct a site audit. This may occur at any time from start to after conclusion of the study.

All documents of this clinical trial (e.g. trial investigator file and documentary sheets) are to be kept in a secure place at the study center for at least 15 years after the final trial report has been published.

## **11 Statistics**

### **Study Aims**

This study is a prospective multisite, non-randomized open single-arm Phase I/II study in children and adults with leukemia and MDS with molecular relapse after allogeneic SCT.

The main purpose of this study is to assess the feasibility and the efficacy of CIK cells infusions to acquire essential information about the practicality of a posterior larger study. In this early stage about CIK cells infusions there are no sufficient information for an initial hypothesis therefore this study is explorative.

### **Exploratory Endpoints**

Efficacy:

- Proportion of patients that achieve complete and partial response after 1 year of first CIK cells infusion.
- Progression-free survival and overall survival
- Response duration

Safety Endpoint:

- Proportion of patients who become aGvHD > grade II or extensive chronic GvHD.

CIK cells infusions:

- The dose-limiting toxicity based on grade III or IV acute GvHD

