Starting T cell dose within CIK cell infusions was 1x10^6 T cells/kg body weight. Regardless of donor type, dose escalation continued up to 1x10^8 T cells/kg body weight if no signs of acute GvHD >grade I occurred. Median doses of infused T cells were 6x10^7 in the matched unrelated and 1x10^7/kg in the haploidentical transplantation setting. Mild signs of acute GvHD occurred in 2 patients (14%).

Another 3 patients (21%) developed acute GvHD grade III with evidence of cutaneous, intestinal and hepatic involvement. All of these high-risk patients had been treated with CIK cells from haploidentical donors prophylactically at a maximum dose of 5x10^6, 5x10^6 and 20x10^6 CD3+CD56 CIK cells/kg body weight. All patients experienced a timely coincident regeneration of CD3+ T cells. Therefore it is not clear whether the occurrence of GvHD is solely attributable to CIK cell infusions. Treatment for acute GvHD included immunosuppressive medications in addition to steroid therapy and infusions of mesenchymal stroma cells. One patient additionally received extra corporal photopheresis. All patients finally recovered from GvHD and remained in complete remission until the last follow-up.

In 6 patients (43%), 3 with overt and 3 with impending relapse, CIK cell infusions temporarily provided stable disease (median 218 days, range 56-563 days), followed by another allogeneic SCT in 2 cases. Deaths of 2 heavily pretreated AML-patients (14%) who remained in remission after CIK cell infusions were not CIK cell-related. Another 6 leukemia patients (43%), 3 of whom were not in remission at the time of SCT, are still in complete remission. All of them were offered CIK cell infusions from haploidentical donors.

Accordingly, Introna, Laport, Linn and colleges described application of donor-derived CIK cells in adult patients with relapsed hematological malignancies after allogeneic SCT. Altogether, serial CIK cell infusions seem to be a promising therapeutic approach for patients being at risk of relapse, provided that CIK cells are administered in high numbers and short-term intervals, early after allogeneic SCT.

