### **2.1 Primary Objectives**

- To assess the safety and feasibility of increasing cell doses of CIK cell transfusions in adult and pediatric leukemia and MDS patients with molecular relapse after allogeneic SCT. The occurrence of grade III or IV acute GvHD and extensive chronic GvHD will be judged being related to the CIK cell intervention. Grading and staging will be performed using the Glucksberg Seattle scale.

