### Confidence intervals for safety

The occurrence of grade III or IV acute GvHD and extensive chronic GvHD will be considered to evaluate the safety in this study. According to published results the aGVHD > Grad II incidence for a patient with DLI treatment can be assumed 40%. We expected a lower incidence rate of aGVHD. We investigated given an incidence rate of having an aGVHD > Grad II equal to 5%, 10%, 20% and 30% then confidence interval width for different two-sided confidence levels in a sample size of 20 patients.

| N  | Rate | CI width 95 | CI width 90 | CI width 68 |
|----|------|------------------------|------------------------|------------------------|
| 20 | 0.05 | 0.247                  | 0.214                  | 0.147                  |
| 20 | 0.10 | 0.305                  | 0.265                  | 0.181                  |
| 20 | 0.20 | 0.379                  | 0.330                  | 0.222                  |
| 20 | 0.30 | 0.424                  | 0.368                  | 0.247                  |
| 20 | 0.40 | 0.448                  | 0.389                  | 0.26                   |
| 20 | 0.50 | 0.456                  | 0.396                  | 0.264                  |

The next figure represents the CI width vs different aGVHD incidence rate for one group (sample size = 20) for different confidence levels.

[figure not shown]

The estimated duration of the recruitment period is equal to 3 years according to our evaluated data in the last 10 years. Each center has treated ca. 6-7 patients per year who fulfilled the inclusion criteria defined in the protocol.

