## Analysis

A descriptive statistics will be performed at the end of the study. An intent-to-treat principle (ITT) or per-protocol analysis will be done.

To analyze the efficacy of CIK cell treatment following factors will be considered:

- Complete and partial molecular response
- rate and duration of complete/partial molecular response following CIK cell administration at the end of CIK cell infusions and after 1 year of first CIK cell infusion
- rate of and time to non response
- rate of and time to relapse with previous partial/complete response
- Progression-Free survival (PFS) and overall survival (OS)
- Cumulative incidences of: haematological relapse/progression, deaths without relapse/progression
- Cumulative incidence of aGVHD > grade II and extensive chronic GvHD
- Median and range for the number of CIK cell dose and for cumulative dose CIK cells/kg for all patients, children and adults

- Median and range for cumulative T cells/kg according donor type (MSD, MUD,MMFD) that patient requires in the study

Complete molecular response is defined as the molecular remission: the Minimal Residual Disease not detectable (MRD < 10^-6) and Mixed Chimerism MC < 1%.

Partial response is defined as no molecular remission but not haematological relapse. Non response is defined as haematological relapse without previous or complete response.

The median of PFS and OS time will be estimated. Kaplan-Meier estimates will be used to estimate PFS probability and OS probability. Log-rank test will be used as appropriate. For PFS will be considered as events: disease progression or relapse, death without relapse/progression and secondary neoplasm. For OS death from any cause will be considered an event.

Gray-Model will be used for cumulative incidences. Patients lost to follow-up without event will be censored at the date of their last follow up evaluation.

PFS, OS and cumulative incidences will be estimated after 1 year initiation of CIK cell therapy and after 1 year until the last CIK cell infusion.

If the data meet the necessary requirements, longitudinal analysis will be conducted to explore the improvement of hematologic and immune reconstitution of leucocyte, CD3-, CD4-, CD8-, CD56-, and CD14-positive cells until the first year after begin of the CIK cells therapy.

The dynamic of cytokine profile during cell infusion and tumor escape mechanisms following CIK cell infusion will exhibit in curves over the time.

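### DLT is a primary endpoint of a trial of increasing doses, but it has no window, dose attribution or denominator per dose step, and no event count triggers a study-level safety review

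*Protocol*

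**What the plan says.** Section 2.1 sets the primary objective: "To assess the safety and feasibility of increasing cell doses of CIK cell transfusions". Section 2.3 names DLT based on grade III or IV aGvHD, and extensive chronic GvHD, as primary endpoints.

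Sections 3.1 and 5.4 describe escalation within each patient: 1x10^6/kg at the first infusion, 5x10^6/kg at the second, 1x10^7/kg from the third, up to 8 infusions at intervals of 4 to 6 weeks. Section 5.4 also allows modified doses for some patients.

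In section 11, Exploratory Endpoints, the safety endpoint is "Proportion of patients who become aGvHD > grade II or extensive chronic GvHD", and a separate line lists "The dose-limiting toxicity based on grade III or IV acute GvHD". Analysis adds cumulative incidences of the two GvHD events. Donor type appears once: "Median and range for cumulative T cells/kg according donor type (MSD, MUD,MMFD) that patient requires in the study".

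Confidence intervals for safety gives the one benchmark, "According to published results the aGVHD > Grad II incidence for a patient with DLI treatment can be assumed 40" per cent, expects a lower rate, and prints interval widths for 20 patients. Section 8.2 lists reasons to end the study in words only, such as "Negative benefit/risk assessment due to new information".

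**The concern.** A trial of increasing doses should be able to say how often DLT followed each dose, and in how many patients that dose was given. Here patients leave before later steps because of aGvHD, response or relapse, so the steps have different numbers at risk. A per-patient summary adds the steps together. With no window and no rule linking an event to an infusion, two analysts could assign the same event to different doses.

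Donor type matters for a similar reason. Of the three grade III cases in the earlier experience (section 1.5), "All of these high-risk patients had been treated with CIK cells from haploidentical donors prophylactically". Two of them had a maximum dose of 5x10^6/kg, the second step here. Section 11 nevertheless does not use donor type for GvHD.

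Finally, a benchmark without a count gives nobody a pre-agreed point at which to look at the accumulating rate. At stake are the answer to the primary objective and a numerical safety signal during the trial.

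**Working it through.** **1. The plan's own figures.** Exact (Clopper-Pearson) intervals with x = N × rate reproduce all 18 safety widths for N = 20 to within 0.001. Example, rate 0.20: 4/20 gives 0.0573 to 0.4366, width 0.379; the 90% and 68% widths are 0.330 and 0.222, as printed.

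**2. What a per-patient figure can distinguish.** Let h1, h2, h3 be the DLT risks at the three steps and assume that every event-free patient goes on. The per-patient risk is 1 − (1 − h1)(1 − h2)(1 − h3). The profiles are assumptions.

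| h1 / h2 / h3 | Per-patient risk |
|---|---|
| 7.17 / 7.17 / 7.17% | 1 − 0.9283³ = 20% |
| 0 / 0 / 20% | 1 − 0.80 = 20% |
| 20 / 0 / 0% | 1 − 0.80 = 20% |

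The planned proportion is the same for all three.

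**3. Precision after a split by dose.** With 0 events among 20 patients at a step the exact 95% upper limit is 16.8%; among 10 it is 30.8%. Numbers per step are assumed, because the protocol gives none.

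**4. Donor type in the earlier experience** (section 1.5: 8 haploidentical, 6 matched unrelated, 3 grade III cases, all haploidentical).

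- Overall: 3/14 = 21.4%, exact 95% CI 4.7 to 50.8%
- Haploidentical: 3/8 = 37.5%, CI 8.5 to 75.5%
- Matched unrelated: 0/6, CI 0 to 45.9%
- Fisher exact p = 0.21

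**5. The 40% benchmark.** It refers to aGvHD above grade II, so the comparison concerns that component alone.

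| Events | Exact 95% CI |
|---|---|
| 3/20 | 3.2 to 37.9% |
| 4/20 | 5.7 to 43.7% |
| 9/40 | 10.8 to 38.5% |
| 10/40 | 12.7 to 41.2% |

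The upper limit is below 40% only with at most 3/20 or 9/40 events. Taking a true rate of 3/14 as an assumption, the binomial probabilities are P(X ≤ 3; n = 20) = 0.35 and P(X ≤ 9; n = 40) = 0.65. The interval lies wholly above 40% only from 13/20 (40.8 to 84.6%) or 23/40 (40.9 to 73.0%). Between those counts it includes 40%.

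**6. A review count, for illustration only.** Trigger a review when P(rate > 40%) ≥ 0.80 under a Beta(0.4, 0.6) prior, checked after every patient from the fourth. With x events in n patients the posterior is Beta(0.4 + x, 0.6 + n − x). The smallest triggering counts are 3/4, 4/5–7, 5/8–9, 6/10–11, 7/12–13, 8/14–15, 9/16–17 and 10/18–20. Exact probabilities of a trigger, where the last column is 1 − (1 − p)² with p the unrounded figure for one group:

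| True rate | One age group of 20 | At least one of two groups |
|---|---|---|
| 10% | 0.6% | 1.1% |
| 21% (3/14) | 7% | 13% |
| 30% | 20% | 36% |
| 40% | 46% | 71% |
| 50% | 75% | 94% |

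**The case against.** The study is declared exploratory and has no hypothesis. Tables by dose or donor type can be left to a SAP, which is not shown. This stands for table layout. It does not cover the definition of a primary endpoint or a count that would govern conduct, both of which belong in the protocol.

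Several stronger readings are tempting, and the documents do not support them.

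- **Safety is one pooled proportion.** DLT and cumulative incidence are listed as well, and precision is given for one group of 20. The fault is that DLT is never made operational.
- **Only patients free of aGvHD reach later steps.** Grade I aGvHD does not stop infusions (section 3), and modified doses are possible (section 5.4), so infusion number need not equal dose step.
- **The overall rate mainly reflects the donor mix.** The contrast is 3/8 against 0/6 with p = 0.21, and all three cases were treated prophylactically, unlike the patients with molecular relapse enrolled here. It is a reason to report by donor type and not evidence of an effect.
- **Nothing would prompt a review.** SAEs reach the sponsor within 24 hours (section 6.2), events altering risk/benefit are reported within 15 days (section 6.3), safety reports are annual (section 6.4), and section 8.2 permits termination. Only a numerical trigger is absent.
- **Upper limits are unavailable.** The efficacy table for n = 20 prints exact limits at the same rates (0.437 at 0.20). What is missing is their use against 40%.
- **A table by dose would show which dose is tolerable.** Dose is mixed with order, cumulative dose and time, so the table stays descriptive.

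**Conclusion.** The point holds in this form: DLT is a primary endpoint without a window, attribution rule or denominator per dose step; donor type is not used for GvHD; and the 40% benchmark carries no decision. Followed as written, the protocol yields no dose-specific DLT result and no numerical safety signal. This can be put right cheaply and should be; it does not invalidate the trial.

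Size: an identical 20% per-patient figure can come from sharply different step risks. An upper limit below 40% has probability 35% with 20 patients and 65% with 40, if the true rate equals the earlier 21%. That rate comes from 14 patients in a partly different setting (CI 4.7 to 50.8%), so these probabilities are indicative.

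A related inconsistency affects who is at risk at later steps. The Synopsis and section 3 withhold the next infusion from aGvHD grade II upward; sections 5.4 and 8.1 stop infusions only above grade II. The passages must be reconciled.

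**What to change.** In sections 11 and 8.2:

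1. Define DLT for analysis. Tabulate grade III or IV aGvHD by the dose actually given at the most recent infusion, with patients infused at that dose as denominator, a fixed window (to the next infusion or 6 weeks, whichever comes first) and exact CIs. Label the table descriptive. Report extensive cGvHD by highest and by cumulative dose received.
2. Report the primary safety endpoints by donor type and by age group with exact CIs.
3. State the upper limit against 40%, and pre-specify an event count per age group that triggers a safety review. The sponsor sets the threshold and gives full operating characteristics, per group and for two groups together. The boundary shown above is an illustration, not a recommendation.
4. Reconcile the aGvHD thresholds for withholding infusions.

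The cost is wording and a running event count, using data already collected. The strata will be small with wide intervals, and there will be some false alarms: with the illustrated boundary, 7% per group and 13% over two groups at a true rate of 21%.

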### **2.3 Primary Endpoints**

- The dose-limiting toxicity based on grade III or IV acute GvHD
- Chronic extensive GvHD

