### 3.1 Study Procedure

FFM – CIK-Cell Study 01, Eudra-CT: 2013-005446-11

[figure not shown]

Figure 1: Trial scheme (new)

In this phase I/II study, adult and pediatric patients with acute leukemia or MDS after allogeneic SCT will be screened for relapse according to general practice including chimerism analyses.

- In patients with impending relapse indicated by MRD levels or MC ≥ 1% including chimerism subpopulations, leukemic blast must be below 5% of cells in bone marrow samples for eligibility.
- Having reached all required inclusion criteria, patients will receive first dose of CIK cell infusions.
- According to risk for GvHD, starting dose will be 1 x 10^6 CD3+CD56 CIK cells/kg in pediatric as well as in adult patients.
- Monitoring for infusion-related reactions will include allergic reactions, cardiac arrhythmia, GvHD and transmission of infectious diseases.  
As anaphylaxis cannot be precluded, CIK cell infusions must be administered where emergency resuscitative equipment and personnel trained in the management of anaphylaxis are immediately available to treat systemic reactions under the direct supervision of a physician. Anaphylaxis and cardiac arrhythmia both may occur while or shortly after infusion (for treatment

recommendations please see 3.2). Therefore, patients should be monitored overnight within the context of an inpatient hospital stay.

GvHD is expected to occur 2-4 weeks after infusion and may be treated by steroids or immunosuppressive medications.

- Before CIK cell infusion, one hour as well as one and two weeks after CIK cell infusion blood will be taken for assessment of blood counts, numbers of CD3-, CD4-, CD8-, CD56-, CD14- positive cells, cytokine profiles and soluble ligands of NKG2D receptor.
- Following CIK cell infusions, patients will be screened for GvHD according to Glucksberg Seattle Criteria (GSC, Appendix 1) every two weeks and will undergo bone marrow assessment every 3 months for efficacy analysis.

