#### Acute Toxic effects

Infusional toxicity is defined as any of the following while and within 60 minutes after CIK cell infusion:

Allergic/hypersensitivity reactions,  
Anaphylaxis,  
Cardiovascular reactions (hypotension, hypertension),  
Respiratory reactions (hypoxia, bronchospasm),  
Neurological reactions (ataxia, encephalopathy and seizures),  
Acute kidney and  
Hepatic toxicities

Toxicity will be graded according to the NCI Common Terminology Criteria for Adverse Events version 4.0 for infusion related reactions, allergic/hypersensitivity reactions, anaphylaxis, cardiovascular (hypotension), respiratory (hypoxia, bronchospasm), neurological (ataxia, encephalopathy and seizures), acute kidney and hepatic toxicities. The criteria is available online at:

[http://evs.nci.nih.gov/ftp1/CTCAE/CTCAE\\_4.03\\_2010-06-14\\_QuickReference\\_8.5x11.pdf](http://evs.nci.nih.gov/ftp1/CTCAE/CTCAE_4.03_2010-06-14_QuickReference_8.5x11.pdf)

As acute toxic effects including anaphylaxis cannot be precluded, CIK cell infusions must be administered where emergency resuscitative equipment and personnel trained in the management of anaphylaxis, cardiovascular, respiratory and neurological reactions are immediately available to treat systemic reactions under the direct supervision of a physician. Therefore, patients should be monitored overnight within the context of an inpatient hospital stay.

Potential risks identified during previous administration of CIK cells – specified in the SmPC of the product – are:

- Infusion-related reactions
- Allergic reactions
- GvHD
- Cardiac arrhythmias
- Transmission of infectious diseases

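### The DLT and safety endpoints count GvHD only, and no mandatory rule withholds the next CIK dose after a severe infusion reaction or arrhythmia

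*Protocol*

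**What the plan says.** Section 2.1 of the protocol sets the primary objective: "To assess the safety and feasibility of increasing cell doses of CIK cell transfusions". It then names the events on which this is judged: "The occurrence of grade III or IV acute GvHD and extensive chronic GvHD will be judged being related to the CIK cell intervention". The primary endpoints in 2.3 and the synopsis follow, with "The dose-limiting toxicity based on grade III or IV acute GvHD" and extensive chronic GvHD. In section 11 the safety endpoint is "Proportion of patients who become aGvHD > grade II or extensive chronic GvHD", and the precision calculation starts from the same events: "The occurrence of grade III or IV acute GvHD and extensive chronic GvHD will be considered to evaluate the safety in this study". The only safety item in the section 11 analysis list is the cumulative incidence of GvHD.

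Other risks are named elsewhere. Section 3.1 states: "Monitoring for infusion-related reactions will include allergic reactions, cardiac arrhythmia, GvHD and transmission of infectious diseases". Under Acute Toxic effects, section 3.2 requires grading: "Toxicity will be graded according to the NCI Common Terminology Criteria for Adverse Events version 4.0 for infusion related reactions". The list introduced there as "Potential risks identified during previous administration of CIK cells" contains infusion-related reactions, allergic reactions, GvHD, cardiac arrhythmias and transmission of infections.

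The dose schedule in 3.1 is fixed within each patient: 1x10^6, then 5x10^6, then 1x10^7 CD3+CD56- cells/kg for the third and all later infusions, at intervals of 4 to 6 weeks and up to 8 infusions.

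**The concern.** The objective covers safety under rising doses, but every defined measure of it covers one toxicity. A patient with grade 4 anaphylaxis and no GvHD is DLT-free and counts as event-free in the section 11 proportion. The protocol grades infusional toxicity but ties no grade to the DLT, an endpoint or a dosing decision.

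The dosing side matters more. If no criterion requires the next infusion to be withheld after a severe first reaction, the written schedule leads to a second dose five times as large, in children as well as adults. Whether it is given then rests on individual judgement at three sites.

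**Working it through.** **1. Does any mandatory rule withhold the next dose after a severe infusion reaction or arrhythmia?** The provisions that could do so are:

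- Section 3 and 3.1: the toxicity condition for the next infusion is acute GvHD below grade II.
- Section 3.2, Infusion-related reactions: the current infusion is stopped for an allergic reaction. Later infusions are not mentioned.
- Section 3.2, requirements for the next infusion: no immunosuppression or steroids, and no chemo- or immune therapy apart from TKI. Steroids given for a reaction would block the next dose only while they continue.
- Section 4.2: hypersensitivity to a component of the product is an exclusion at entry and is not repeated before later doses.
- Section 5.4: modified doses are foreseen for disease progression or low-grade acute GvHD.
- Section 8.1, stop of infusions with the patient staying in the study: GvHD above grade II, response, severe infections.
- Section 8.1, withdrawal: pregnancy, or relapse needing other treatment.
- Section 8.1, opening: the investigator may withdraw a patient for adverse events. This is a right, not a requirement.
- Section 8.2: the whole study may be ended for safety reasons, with no threshold.

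None is a mandatory bar. Severe infection is already a non-GvHD stop criterion, so the list is not confined to GvHD by design.

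**2. Dose steps (section 3.1).** Second over first: 5x10^6 / 1x10^6 = 5. Third over second: 1x10^7 / 5x10^6 = 2. Overall: 1x10^7 / 1x10^6 = 10. After an event at the third or a later infusion, the next dose is the same, not higher.

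**3. The plan's own precision figures.** Exact (Clopper-Pearson) intervals reproduce all 18 widths in the section 11 safety table. For example, 4/20 gives 0.057 to 0.437, width 0.379 as printed. The arithmetic is sound; the question is what is counted.

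**4. Weight of one uncounted patient.** 1/20 = 5.0 percentage points; 1/40 = 2.5 percentage points.

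**5. What a separate infusional component would show (assumed counts, n = 20, exact 95% CI).**

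- 0/20: 0%, upper limit 16.8%
- 1/20: 5%, 0.1% to 24.9%
- 2/20: 10%, 1.2% to 31.7%

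**6. Chance of at least one such event (assumed true rate q per patient).** P = 1 - (1 - q)^n.

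- q = 5%: 64% in 20 patients, 87% in 40
- q = 10%: 88% in 20, 98.5% in 40
- q = 20%: 99% in 20, above 99.9% in 40

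**7. Effect on a DLT rate (assumed GvHD rate g = 10%, independent of q).** 1 - (1 - g)(1 - q) gives 14.5%, 19% and 28% for q = 5%, 10% and 20%, against 10% when only GvHD counts. The documents give neither rate, so this shows a range and is not an estimate.

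**The case against.** The GvHD endpoint is a declared choice, applied consistently in 2.1, 2.3 and section 11. It is also a sensible lead risk. In the group's own series (section 1.5), 3 of 14 patients (21%) had grade III acute GvHD over 58 infusions, and no severe infusional event is described, although none is ruled out. GvHD is also the risk on which CIK cells are weighed against DLI. All of this stands, and it is why the GvHD endpoint should stay as it is.

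A reader might infer that a severe infusion reaction escapes the safety evaluation. The documents do not support that. Such events are graded, all clinical AEs go on the CRF (6.1), and SAEs are reported to the sponsor within 24 hours whatever the causality (6.2). AE tables may be left to a SAP that is not shown. What is missing is an endpoint or DLT that counts these events.

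A reader might also infer that nothing can prevent the next dose. That goes too far: section 3.3 ends infusions when the 8.1 discontinuation criteria are met, and 8.1 opens with the right to withdraw a patient for adverse events. Section 3.2 also refers to product information that is not at hand and may address re-dosing. But the stated right is discretionary and concerns leaving the study. Under 3.3 off-protocol patients are followed for 28 days, whereas those who only stop infusions are followed for a year. A patient withdrawn for a reaction could therefore lose most of the follow-up for chronic GvHD.

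Finally, infection is a named risk that the GvHD endpoints also leave out. It already has a stop criterion in 8.1, so the dosing gap does not apply to it.

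**Conclusion.** The point holds, at moderate weight. The DLT and every defined safety endpoint count GvHD only, although the objective is safety under increasing doses and the protocol names infusion-related reactions, allergic reactions and arrhythmias as product risks. No mandatory criterion withholds the next infusion, up to 5 times larger, after a severe event of this kind.

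The size is unknown because the documents give no rate for such events. The firm figures are the weight per patient (5.0 percentage points in 20, 2.5 in 40) and the dose steps (5-fold, then 2-fold). The remaining figures rest on assumed counts or rates.

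Two stronger conclusions might be drawn and are not supported. The section 11 GvHD proportion is not biased: it estimates what its label says, and it falls short only as a summary of overall safety. Dose escalation between patients is not distorted either, because the DLT feeds no cohort or MTD rule. DLT definitions and stop criteria govern dosing and belong in the protocol, so this is more than detail left to a SAP.

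**What to change.** 1. In 8.1, add to the criteria that stop infusions while the patient remains in the study: a CTCAE grade 3 or higher infusion-related or allergic reaction, or cardiac arrhythmia, at least possibly related to CIK cells. Name arrhythmia explicitly, because the definition of infusional toxicity in 3.2 does not list it. State the time window as well: 3.2 uses 60 minutes, while the schedule legend in the synopsis has monitoring up to 12 hours. If re-treatment is wanted, state instead in the 3.2 requirements for the next infusion that it is withheld until the event has resolved and is not given at a higher dose.

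2. In 2.3, the synopsis and section 11, count these related events as DLTs. Report their proportion by age group with exact 95% CIs, as a separate safety component beside the unchanged GvHD endpoint. Compare only acute GvHD above grade II with the 40% assumed for DLI.

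The cost is wording in those sections and a few tables. The data are already collected at each infusion and on the AE and SAE forms. A few patients may stop infusions earlier, and the reported safety profile may look slightly less favourable.
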